### Aims and objectives

The primary objective will be to evaluate the efficacy of CBT for loneliness in children and young people ages 11–18. The primary outcome will be differences in scores on the Three-Item Loneliness Scale [34] between baseline and intervention and baseline and post-intervention. It is hypothesised that there will be a significant decrease in self-reported loneliness across both time-points. The secondary outcomes will be self-reported loneliness scores on the UCLA Loneliness Scale (UCLA-LS-3) [35] and self and parent-reported scores on the Strengths and Difficulties Questionnaires (SDQ) [36] and Revised Child Anxiety and Depression Scale (RCADS) [37]. It is hypothesised that there will be a reliable and clinically meaningful change [38] in total loneliness scores on the UCLA-LS-3, in the impact scores on the SDQ and in total anxiety and depression scores on the RCADS.

The secondary objective is to evaluate the feasibly and acceptability of the intervention process. This will be defined in terms of a) meeting the recruitment target, b) participant retention and c) participant feedback of the intervention using the Experience of Service Questionnaire [39].

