**Fig 1 pone.0278746.g001:**
[figure not shown]
Showing the trials schedule of enrolment, interventions and assessments.

Participants will be recruited via advertisements emailed to schools, shared via social media and word of mouth. Participants and their parents/carers will be sent an electronic information sheet and given the opportunity to ask any questions before completing an online consent form. Participants will provide informed ascent as they are under 18, with parents/carers providing informed consent. Participants and their parents/carers will then complete a baseline eligibility assessment. They will complete a range of online questionnaires via Qualtrics [41], a secure online platform. They will then attend a remote research assessment appointment to determine whether the family meet the eligibility criteria. The researcher completing the baseline and post-intervention assessments will not be involved in the clinical intervention and will be blinded to baseline allocation. After all baseline assessments for the participant group are completed, they will be discussed within supervision to confirm that the participants meet eligibility criteria. Eligible participants will then be randomised using a random number generator to one of four different baseline lengths (12 days, 19 days, 26 days or 33 days [42]. The decision to have a minimum of 12 observations per phase meets the requirements for guidelines and standards [43] and will allow for sufficient power for Tau-U analysis [44, 45].

Each of the families will then be contacted to inform them of their allocation. Randomisation and contacting of the families will be completed by a third researcher, who is not involved in either the clinical intervention or research assessments. Families will receive a £25 voucher for completing the baseline eligibility assessment. A letter will also be sent to their General Practitioner (GP) informing them of the family’s participation in the research study. The setting for the entire study will be remote via Zoom [46], with participants recruited from across the United Kingdom (UK).

All participants in the group will begin their baseline phase concurrently. During the baseline phase participants will be asked to complete the Three-Item Loneliness Scale [34] each day via Qualtrics [41]. SMS message reminders will also be sent to the young people and their parent/carers each day.

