The baseline phase will be immediately followed by the intervention. Each family will receive (on average) 12 sessions of CBT for loneliness in children and young people. Where possible the first 4 sessions will take place bi-weekly, the second 4 sessions weekly and the final 4 sessions fortnightly.

For all participants the first two sessions will be focussed on assessment and then formulation. The final session for all participants will focus on relapse prevention. During the assessment session the participant will be asked to define 3 goal-based outcomes (GBOs) [47] for how they hope the intervention will reduce their loneliness, which will then guide the treatment process. During the intervention phase the participants will complete routine outcome measures (ROMs) for each session. This will include the Three-Item Loneliness Scale [34], visual analogue scales (VAS) of mood, anxiety and loneliness and ratings of their goal-based outcomes [48]. The ROMs will be completed via Qualtrics [41] before each session. If participants have not completed the ROMs before their appointment, then they will be completed with the clinician at the start of the session.

Participants will begin the post-intervention phase immediately after the final session of their intervention. During the post-intervention phase participants will be asked to complete the primary outcome measure, Three-Item Loneliness Scale [34], each day for 12 days. They will then complete their post-intervention assessment with the second researcher. Before the assessment they will be asked to re-complete the baseline questionnaires in addition to the parent and child-report versions of the Experience of Service Questionnaire [39] and a questionnaire asking whether COVID-19 or any other events have affected them during the intervention period. The family will be given a £25 voucher for completing the post-intervention assessment. A letter will be sent to their General Practitioner (GP) informing them of their participation in the research study has finished.

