### Procedural fidelity

The intervention will be conducted by the first author (TC). He will receive weekly supervision from RS, AK and SB throughout the research and intervention process to ensure fidelity to the agreed protocol. Procedural fidelity during the intervention phase will also be monitored through the completion of adherence to the manual checklists after each intervention appointment.

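### In the intervention phase only, late primary-outcome ratings are completed with the treating clinician, so a change of measurement mode can start at the phase boundary and bias the baseline-versus-intervention contrast

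*Protocol article*

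**What the plan says.** Aims and objectives defines the primary outcome as "differences in scores on the Three-Item Loneliness Scale [34] between baseline and intervention and baseline and post-intervention". There are thus two primary contrasts on one self-report scale, scored 0–12 with higher meaning lonelier.

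The Procedure section describes how the scale is collected in each phase:

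- **Baseline:** daily, online through Qualtrics. The only prompt described is by text message: "SMS message reminders will also be sent to the young people and their parent/carers each day".
- **Intervention:** the scale is one of the routine outcome measures (ROMs) for each session: "This will include the Three-Item Loneliness Scale [34], visual analogue scales (VAS) of mood, anxiety and loneliness", together with goal ratings. The default is "The ROMs will be completed via Qualtrics [41] before each session". The fallback is "If participants have not completed the ROMs before their appointment, then they will be completed with the clinician at the start of the session".
- **Post-intervention:** "Three-Item Loneliness Scale [34], each day for 12 days", with no clinician route described.

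Procedural fidelity identifies the clinician: "The intervention will be conducted by the first author". The researcher kept apart from the therapy covers the baseline and post-intervention assessments, not the session ROMs.

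The Data analysis section applies Tau-U to both contrasts, allowing for baseline trend, and also reports a weighted average across cases. As described, it does not separate assisted from unassisted readings.

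**The concern.** The clinician route opens when treatment starts, and it does so in every participant. Someone aged 11–18 who rates loneliness with their own therapist present, alongside ratings of goals set with that therapist, may answer differently from someone answering alone on a phone.

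The design's two protections do not reach this. Staggered baselines guard against events tied to calendar time, but a mode change tied to treatment start moves with each participant's own start. Tau-U's baseline-trend correction deals with drift during baseline, not with a step that begins after it.

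If assisted ratings tend to be lower, Tau-U counts the difference as improvement. At stake is how a positive baseline-versus-intervention result can be read, above all in the weighted average, where a shift in the same direction in every case accumulates.

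**Working it through.** The protocol gives no power, alpha or effect-size figure for this contrast, so there is nothing of its own to reproduce. The check compares the modes by phase and then sizes the effect under stated assumptions.

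**Mode by phase**

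| Phase | Frequency | Stated route | Clinician route |
|---|---|---|---|
| Baseline | daily, 12/19/26/33 days | Qualtrics | none described |
| Intervention | per session, 12 on average | Qualtrics beforehand | yes, if not done |
| Post-intervention | daily, 12 days | not named in Procedure; Qualtrics under Data management | none described |

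Only baseline versus intervention can mix modes.

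**Inputs from the protocol:** baseline lengths n_A of 12, 19, 26 and 33; n_B = 12 session readings; 6 to 8 participants; integer scale 0–12.

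**Assumptions, not in the protocol:** no treatment effect; independent readings; SD 1.5; a share of session readings assisted, each 0.5 or 1.0 point lower; inverse-variance pooling; z > 1.96 in the direction of improvement (nominal 2.5%). Baseline-trend correction was not simulated.

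**Formulas:** Tau = S/(n_A·n_B), where S is the number of baseline–intervention pairs that improve minus the number that worsen. Var(S) = n_A·n_B·(n_A+n_B+1)/3. The weight of a case is 1/Var(Tau) = 3·n_A·n_B/(n_A+n_B+1).

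**Tau needed to reach z = 1.96**

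- Weights: 3×144/25 = 17.28; 3×228/32 = 21.38; 3×312/39 = 24.00; 3×396/46 = 25.83. Sum 88.48.
- One case, 12 baseline days: 1.96/√17.28 = 0.47. With 33 days: 1.96/√25.83 = 0.39.
- Six cases (the four lengths plus a second 12 and 19): 88.48 + 17.28 + 21.38 = 127.14, so 1.96/√127.14 = 0.17.
- Eight cases: 2 × 88.48 = 176.96, so 1.96/√176.96 = 0.15.

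With a 1-point shift and SD 2, the simulated spurious Tau averages about 0.07 when 3 of 12 readings are assisted and 0.13 when 6 of 12 are. That is far below the single-case thresholds but close to the pooled ones, so the effect is small per case and larger when pooled.

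**Simulated false-decrease rates (SD 1.5, shift 0.5 to 1.0 point)**

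| Share assisted | Average shift over the phase (share × shift) | Pooled, 6 cases | Pooled, 8 cases |
|---|---|---|---|
| none | 0 | about 2.3% | about 2.3% |
| 1 in 12 | 0.04–0.08 | about 3–5% | about 3–5% |
| 25% | 0.125–0.25 | 7–16% | 8–21% |
| 50% | 0.25–0.50 | 16–51% | 21–67% |

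For a single case at 25% assisted the rate is about 3.5–5.6%. At SD 2 the pooled rates at 25% fall to about 5–11% (6 cases) and 7–13% (8 cases).

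**The case against.** The strongest reply is that this is a fallback. The default is unaided online completion before the session, and nothing says the fallback will be common. At 1 rating in 12 the pooled inflation is small. The upper figures need half of all ratings assisted and every one of those shifted a full point in the same direction. The design is also meant to test effects in individual participants, with visual analysis alongside, and there the inflation is slight. All of this stands, and it limits the size of the point.

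Three stronger readings are tempting, but the document does not support them.

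- **That the therapist takes the primary outcome.** Completing a measure with the clinician may mean only that the young person fills in the form during the call, and the Data management section says participants complete questionnaires via Qualtrics. Administration by the therapist is one possible reading, not a stated fact.
- **That the trial's overall efficacy conclusion is exposed.** It is not: baseline versus post-intervention has no clinician route, so an artefact arising only from this route should not appear in that contrast.
- **That answers will be more favourable.** This is plausible but not shown. A young person might equally disclose more loneliness to a therapist, which would bias against treatment.

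It can also be said that a mode field and a sensitivity analysis are details for a full protocol or analysis plan. On their own they would be no finding. The clinician-completion rule, however, is stated in the article and can be judged as written.

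**Conclusion.** The point holds in a limited form. The stated procedure allows a change of measurement mode that begins at each participant's own phase boundary and could bias one of the two primary contrasts, baseline versus intervention. Neither the staggered baselines nor the trend correction removes it.

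The size depends on how often the fallback is used and on the direction and size of any shift, none of which the protocol gives. Under the assumptions above it runs from negligible (about 3–5% pooled, against a nominal 2.5%, at 1 rating in 12) to serious (16–67% when half are assisted), and it is always smaller for a single case. It is worth correcting because the correction costs almost nothing and because, without a record of mode, nobody could judge the bias afterwards. It does not undermine baseline versus post-intervention.

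**What to change.** Replace the clinician-completion sentence in Procedure. Any Three-Item rating not done beforehand should be completed by the participant alone, through their own Qualtrics link, at the start of the call, with the clinician unable to see the responses. This keeps the purpose of the fallback, which is to avoid losing the reading.

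Record the mode of each rating. Repeat the baseline-versus-intervention Tau-U, per case and pooled, without any clinician-assisted readings. Interpret a baseline-versus-intervention effect alongside baseline versus post-intervention, which this route does not touch.

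The cost is a few minutes of a session, one data field and one sensitivity analysis. The step does not remove other differences between phases, such as participants knowing that they are in treatment.

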### Procedural fidelity

The intervention will be conducted by the first author (TC). He will receive weekly supervision from RS, AK and SB throughout the research and intervention process to ensure fidelity to the agreed protocol. Procedural fidelity during the intervention phase will also be monitored through the completion of adherence to the manual checklists after each intervention appointment.

### Participants

We will aim to recruit 6–8 participants to the study. All participants will be recruited from within the United Kingdom. Participants must meet the following inclusion/exclusion criteria:

#### Inclusion criteria

Aged 11–18Score more than 42 on the UCLA-LS-3 [35], which is more than one standard deviation above the mean in a large community adolescent sample [49].Have a parent/carer who is willing to take part in the study.Report loneliness as their primary difficulty (i.e., they are able to identify relevant goal-based outcomes and their current difficulties are not attributable to a significant mental health problem).

#### Exclusion criteria

Currently receiving psychological therapy.Started taking antidepressant in the last 8 weeks.Eligibility assessment indicates a severe mental health problem not considered suitable for the trial intervention due to the clinical need for immediate intervention, e.g., active suicidality or psychosis.Refusal for therapy sessions to be video recorded.Having an intellectual disability at a level whereby they cannot access the intervention.Do not have access to a laptop or smartphone which they can use for video calls.

### Intervention

To the best of our knowledge this is the first study to examine the efficacy of cognitive behavioural therapy for loneliness in children and young people. The intervention has been developed for this research study using a modular approach based upon Käll et al.’s [23] modular cognitive behavioural formulation. It incorporates translated elements of Käll et al., [25] online intervention, and is informed by the Modular approach to therapy for children with anxiety, depression, trauma, or conduct problems (MATCH-ADTC) [50], Groups4Health [51], PEERS social skills training [52], CBT for Social Anxiety Disorder for adolescence [53] and the literature implicating social camouflaging in mental health difficulties for those on the autism spectrum [54].

The intervention is being developed iteratively based upon feedback and clinical experience using PDSA cycles [31]. The current manual is comprised of 10 treatment modules (Table 1). All participants will complete Module 1 (Assessment), Module 2 (Formulation and Psychoeducation) and Module 10 (Relapse prevention). Other intervention modules will be chosen in collaboration with the participants based upon their personalised formulation and treatment goals. The number of sessions delivered for each module will be determined by treatment priorities, individual progress and the number of sessions remaining. The intervention will be delivered by the first author (TC) who is a trainee clinical psychologist. He will receive weekly supervision from the other authors (RS, AK, SB) who are all qualified clinical psychologists. If there is deterioration in wellbeing or risk issues are identified local statutory or healthcare services will be contacted as appropriate. Participants are able to withdraw from the trial at any time.

**Table 1 pone.0278746.t001:** Showing the treatment modules which comprise CBT for chronic loneliness in children and young people.

Module	Description
1. Assessment	The aim of this module is to complete a structured CBT assessment of the participants loneliness. The CBT assessment will cover each of the modules within Käll et al., [23] formulation. The assessment will also include questions regarding the participants development/early experiences, current living situation, education, physical health, lifestyle (diet, sleep, exercise, hobbies/interests, social media use) and a risk assessment, before identifying three goals for treatment.
2. Formulation and psychoeducation	The aim of this module is to collaboratively complete a modular formulation of the factors maintaining the participants chronic loneliness [23]. The participant will also be given psychoeducation on loneliness, the intervention process and will collaboratively develop a treatment plan based on their formulation and goal-based outcomes.
3. Challenging negative interpersonal appraisals and counterproductive behaviours	The aim of the module is to change the negative thought patterns and counter-productive behaviours which are maintaining chronic loneliness. Participants will be given psychoeducation on the CBT model and the relationship between thoughts, behaviours, physical feelings, and emotions. Participants will be supported to identify the negative interpersonal appraisals and counterproductive behaviours which are maintaining their loneliness. The participant will then be supported to develop within-session behavioural experiments to challenge the counterproductive processes that are maintain their loneliness, which will then be reinforced through agreed homework tasks.
4. Challenging negative thoughts and cognitive biases	The aim of the module is to challenge the negative cognitions and cognitive biases that are maintaining chronic loneliness. Participants will be given psychoeducation on automatic thought processes, negative thinking traps and their role in chronic loneliness. The participant will be supported to develop strategies to challenge thinking errors. The module is based upon the Cognitive Coping modules of MATCH-ADTC [50].
5. Challenging self-focussed attention, hypervigilance and camouflaging	The aim of the module is to challenge self-focussed attention, hypervigilance and/or camouflaging when they are maintaining chronic loneliness. The module is comprised of three submodules: 5A, Reducing Self-Focussed Attention, 5B Reducing Hypervigilance and 5C Reducing Camouflaging Behaviours. Each submodule provides psychoeducation on the role of that difficulty in maintaining chronic loneliness. The participant will then be supported to develop within-session behavioural experiments to challenge the counterproductive processes, which will then be reinforced through agreed homework tasks. Module 5A is based upon CBT for Social Anxiety in Adolescence [53], with module 5B being a hypervigilance-focussed adaptation of this. Module 5C is a novel module informed by the literature regarding the role of camouflaging in mental health difficulties in those on the autism spectrum [54].
6. Values-based social skills training	The aim of this module is to identify the participants social communication strengths and areas for development. The participant will then be supported to develop their social skills in line with their values and treatment goals aiming to reduce their loneliness. The module is informed by the UCLA PEERS program [52] and the social skills module of the internet-based CBT for loneliness in adults [24]. The module is comprised of four submodules: 6A Conversation skills, 6B Managing Teasing and Bullying, 6C Managing disagreements and 6D Dating and Flirting. An emphasis on remote communication is embedded across all submodules.
7. Problems solving	The aim of the module is to teach formal problem-solving to overcome practical barriers to reducing loneliness. The module is based upon the Problem-Solving module within MATCH-ADTC [50]. Participants will be provided with psychoeducation on the problem-solving STEPS before having the opportunity to practice the skills within the session. The participant will then be supported to use the problem-solving skills to overcome the practical barriers that are maintaining their loneliness.
8. Finding Friends	The aim of the module is to map the young person’s current social world and identify opportunities for the development of positive social relationships. Participants will be supported to map their current relationships and rate them in terms of positivity, similarity, support and time spent together. Participants will then link their current social groups based on compatibility. Participants will then be supported to identify strategies to improve their connection with current groups, as well as develop connections with new social groups. The module is informed by the Groups4Health intervention [51].
9. Managing Emotions	The aim of the module is to develop strategies to manage emotional responses where they are maintaining chronic loneliness. The module is comprised of two submodules; 9A: Activity selection (for low mood) and 9B Learning to relax (for anxiety management). Both submodules are based on MATCH-ADTC [50].
10. Relapse Prevention	The aim of the module is to develop a relapse prevention plan with the young person and their parent/carer. This will focus on what the family has learnt during the sessions, strategies to maintain their progress and overcome future difficulties and the difference between a lapse and relapse. Participants will be supported to complete a written plan in addition to a relapse prevention video.

### Outcome measures

#### Loneliness

*The three item loneliness scale [34].* This will be used to assess the child/young persons’ self-reported loneliness throughout each of the three phases of the study. The scale is a brief 3-item measure derived from the UCLA-LS-3 [35]. The measure contains three items rated on a 5-point Likert scale (0 = never, 1 = rarely, 2 = sometimes, 3 = often, 4 = very often). Answers are summed to a total score of 0–12, with higher scores indicating a higher level of loneliness. The Office for National Statistics (ONS) have validated a 3-reponse version of this measure with young people ages 10–15 [19]. In qualitative testing of the measure, they identified that the words “companionship” and “isolation” were difficult for some young people to understand. These changes in wording were also used in this study as the age range was similar to that used in the ONS validation. The items used were “How often do you feel that you have no one to talk to?”, “How often do you feel left out?” and “How often do you feel alone?”.

*UCLA Loneliness Scale (UCLA-LS-3) [35].* The measure will be used to assess the child/young person’s subjective experience of loneliness. The instrument consists of 20 items measured on a 4-point scale where the respondents are asked to indicate how frequently the statement is descriptive of them with the options of never, rarely, sometimes, and often. The UCLA-LS-3 has been used extensively in loneliness research, including in intervention studies [25, 55] and has been validated in a large adolescent sample [49]. The psychometric properties include a very high internal consistency (Cronbach’s α’s ranging from .89 to .94) and a good test-retest-reliability (.73 over a 1-year period) [35].

